## Abstract

**Background:**

The high rate of attrition along the care cascade of infection with human immunodeficiency virus (HIV) results in lost opportunities to provide timely antiretroviral therapy (ART) and to prevent unnecessarily high mortality. This study aims to assess the effectiveness of a structural intervention, the one-stop (“One4All”) strategy that streamlines China’s HIV care cascade with the intent to improve testing completeness, ART initiation, viral suppression, and mortality.

**Method:**

A two-arm, cluster-randomized controlled trial was implemented in twelve county hospitals in Guangxi China to test the effectiveness of the One4All strategy (intervention arm) compared to the current standard of care (SOC; control arm). The twelve study hospitals were selected for homogeneity and allocated one-to-one to the intervention and control arms. All patients screening HIV positive in study hospitals were enrolled. Target study enrollment was 180 participants per arm, 30 participants per hospital. Basic demographic information was collected as well as HIV risk behavior and route of infection. In intervention hospitals, patients then went on to receive point-of-care CD4 testing and in-parallel viral load (VL) testing whereas patients in control hospitals progressed through the usual SOC cascade. The primary outcome measure was testing completeness within 30 days of positive initial HIV screening result. Testing completeness was defined as receipt of all tests, test results, and post-test counseling. The secondary outcome measure was ART initiation (receipt of first ART prescriptions) within 90 days of positive initial HIV screening result. Tertiary outcome measures were viral suppression (≤200 copies/mL) and all-cause mortality at 12 months.

**Discussion:**

We expect that this first-ever, cluster-randomized controlled trial of a bundle of interventions intended to streamline the HIV care cascade in China (the One4All strategy) will provide strong evidence for the benefit of accelerating diagnosis, thorough clinical assessment, and ART initiation via an optimized HIV care cascade. We furthermore anticipate that this evidence will be valuable to policymakers looking to elevate China’s overall HIV/AIDS response to meet the UNAIDS 90-90-90 targets and the broader, global goal of eradication of the HIV/AIDS epidemic.

**Trial registration:**

ClinicalTrials.gov #NCT02084316. (Registered on March 7, 2014)

## Background

In both resource-rich and resource-limited settings alike, patients are commonly lost at each step along the care cascade of infection with human immunodeficiency virus (HIV) that causes acquired immunodeficiency syndromes (AIDS) [1]. In China, the current standard-of-care (SOC) patient pathway from screening HIV-positive to initiating antiretroviral therapy (ART) involves multiple hospital visits, during which patients submit to several separate blood draws, and then experience protracted waiting periods before they are notified of results. This causes substantial loss to follow-up, delays in diagnosis, clinical assessments that are incomplete, and ART initiation at later stages of disease progression [2, 3]. Recent studies have indicated that, in some parts of China, only approximately 43% of those who screen HIV-positive in hospital settings received confirmatory testing [3], and only 57% of those confirmed HIV-positive received CD4 testing within 6 months [4]. Since CD4 count has been used to determine eligibility for ART, it has been estimated that nearly 80% of those with newly-identified HIV infection, who were ART-eligible, were not initiated on ART in a timely fashion. Unfortunately, these missed opportunities for engagement in the HIV care cascade has ultimately translated to preventable high mortality [2, 5].

Although it seems obvious, it is critically important that people living with HIV (PLHIV) step through all the milestones on the HIV care cascade in order for to fully realize the benefits of ART—they must become aware of their HIV-positive status, receive a diagnosis and clinical assessment, attend counseling, enroll in care and initiate ART, and adhere to their treatment regimens and follow-up schedules [1, 6]. However, merely accessing these services, and sequentially stepping through the process, may not be enough. Increasing evidence has highlighted the importance of the timing in which these services are accessed. Two large, recently-completed clinical trials, TEMPRANO and START, have provided evidence of benefit in not waiting to treat HIV infection until evidence of disease progression is present in the form of symptoms or low CD4 count [7, 8]. This benefit of reduced clinical disease progression, as well as decreased overall mortality, has since been confirmed in other settings, including China [2]. In response, the World Health Organization (WHO) modified its guidelines in 2015, recommending immediate ART initiation for all PLHIV regardless of symptoms or CD4 count [9].

The strong evidence for the clinical benefit of immediate ART for PLHIV [7, 8], taken together with the previously-identified public health benefit in the form of reduced transmission rates [10, 11], meant that optimization of the HIV care cascade was even more important than previously thought. A number of studies in a variety of settings have been designed to examine a range of interventions intended to improve the HIV care cascade. Thus far, majority of these types of studies in low- and middle-income settings have been in Sub-Saharan Africa [12]. However, in general, they have not followed participants beyond the pre-ART period and have not evaluated the effectiveness of multiple interventions implemented as a package [13–19]. One such study has recently been completed and published in China, providing evidence that a simplified test-and-treat intervention can improve both HIV care cascade retention and time to ART initiation [2].

### Objective and outcomes

The objective of the present clinical trial was to evaluate a streamlined pathway for patients from screening HIV-positive to initiating ART, testing the effectiveness of a structural intervention—called the one-stop (“One4All”) strategy. This experimental strategy consisted of a new algorithm incorporating rapid, point-of-care (POC) HIV screening and CD4 testing, and in-parallel plasma viral load (VL) testing to promote fast and complete HIV diagnosis and staging, followed by immediate counseling and ART initiation for eligible patients. The One4All intervention was compared to the current SOC (control arm), and four outcomes were assessed:Testing completeness within 30 days of HIV-positive screening (primary)ART initiation within 90 days of HIV-positive screening (secondary)Viral suppression (≤200 copies/mm^3^) at 12 months after HIV-positive screening (tertiary)All-cause mortality at 12 months after HIV-positive screening (tertiary)

## Method

### Design

A cluster-randomized trial was designed as diagrammed in Fig. 1. Hospitals were the unit of randomization and twelve similar county-level hospitals were allocated one-to-one to the intervention and control arms of the study. The efficacy of the intervention was determined by comparison to the current standard of care (SOC, control arm) at 30 days, 90 days, and 12 months.

**Fig. 1 Fig1:**
[figure not shown]
Diagram of study design. This diagram illustrates the cluster-randomized controlled study design with one-to-one allocation of twelve county-level hospitals to either the control arm (current standard of care [SOC]) or the intervention arm (the “One4All” strategy intended to streamline the HIV care cascade)

### Setting

The setting for this study was county hospitals in Guangxi Zhuang Autonomous Region (hereafter referred to as Guangxi). In 2011, Guangxi reported the second highest cumulative number of HIV/AIDS cases in China, the highest number of newly-reported HIV/AIDS cases, the highest number of newly-reported AIDS cases, and the highest number of AIDS-related deaths [5]. As shown in Fig. 2, a broad range of characteristics of potential county-level hospitals in Guangxi were examined. The hospitals included in the study were selected based on their homogeneity across these characteristics.

**Fig. 2 Fig2:**
[figure not shown]
List of Hospital Characteristics. The eighteen different characteristics listed here were examined in the process of assessing candidate county-level hospitals in Guangxi, China. The final twelve study hospitals were selected based upon homogeneity across these characteristics

### Allocation and blinding

The twelve selected study hospitals were stratified by historical rates of testing completeness followed by post-test counseling during the first six months of 2013 prior to being allocated to the intervention or control study arms. Eight hospitals were within the low historical testing completion stratum of <20%, and these eight hospitals were randomized, four into the intervention arm and four into the control arm. Four hospitals were within the high historical testing completion stratum of ≥20%, and these four hospitals were randomized, two into the intervention arm and two into the control arm. All patients who screened HIV-positive in the six intervention hospitals received the One4All intervention and all patients who screened HIV-positive in the six control hospitals during the same study period received SOC services. There was no blinding required since the unit of randomization was the study hospital and each hospital only offered the HIV care cascade it was assigned during randomization—SOC or One4All.

### Participants and recruitment

Study eligibility criteria were: [a] being 18 years of age or older, [b] having a positive result on an HIV enzyme immunoassay (EIA) screening test, [c] seeking care in a study hospital, either inpatient or outpatient, and [d] residing or intending to reside within the study catchment area. Study exclusion criteria were: [a] having previously received confirmation of HIV infection in any setting, [b] being a prisoner or detainee at time of screening, or [c] being a pregnant woman.

No special strategies to ensure adequate participant enrollment were employed. All patients who were found to be eligible were enrolled in the study. After enrollment, basic demographic information was collected. Information on self-reported risk behavior and route of HIV acquisition were also collected.

### Ethics

The protocol and consent process were reviewed and approved by the US National Institutes of Health (NIH), National Institute on Drug Abuse (NIDA) Protocol Review Board and Data and Safety Monitoring Board, as well as respective institutional review boards (IRBs) of the University of California, Los Angeles (UCLA) and the National Center for AIDS/STD Control and Prevention (NCAIDS), China Center for Disease Control and Prevention (CDC).

Individual informed consent was not obtained. Study information was shared with participants and participants were given opportunities ask questions. While participants could refuse to participate, or to share their data, their enrollment still counted toward the total number of study participants. No study-related reimbursement for participants was provided.

All patient data were protected and kept confidential according to standard procedures present within China’s healthcare system. Participant data extracted from hospital records, and from China’s National HIV/AIDS Comprehensive Response Information Management System (CRIMS, which has been described elsewhere) [20], were assigned trial-specific participant identification numbers and then otherwise de-identified prior to use to protect participant privacy.

### Sample size

A minimum sample size of 180 participants per arm, across 12 clusters (or 30 participants per cluster) was selected. This sample size was expected to achieve 93% power based on a one-sided test (at alpha = 0.05) to detect a difference between the group proportions of 0.28, where under the alternative hypothesis the One4All arm proportion was assumed to be 0.50 and the control arm proportion was assumed to be 0.22. This calculation assumed an intra-class correlation (ICC) within hospitals of 0.082 based on preliminary data. Although 30 participants per cluster (or hospital) was the target, it was expected that some hospitals would enroll participants more quickly than others. Therefore, a final study population of greater than 180 participants per arm was anticipated as enrollment at all hospitals remained open until the last hospital met its 30-participant goal.

### Intervention

A high-level overview of the HIV care cascade in SOC (control arm) and One4All (intervention arm) hospitals is depicted in Fig. 3. The One4All test intervention included rapid, POC HIV EIA screening and CD4 testing, with in-parallel VL testing. This strategy was intended to promote rapid and complete diagnostic assessment and accelerate time to ART initiation for those deemed ART eligible. The ART eligibility threshold at the time of this study was CD4 count ≤350 cells/mm^3^. Each of the steps in the HIV care cascade up to assessment of ART eligibility are described in detail below for both the SOC condition and the One4All condition. In both care cascades, all participants received post-test counselling each and every time they received test results.

**Fig. 3 Fig3:**
[figure not shown]
Illustration of Intervention and Control Conditions. This illustration depicts the differences in the HIV care cascade between control (standard of care [SOC]) and intervention (“One4All” strategy) study arms. In the SOC condition, HIV care cascade steps 2, 3, 4, 5, and 7 are all consolidated into a single step 2 in the One4All condition

#### HIV Screening

*In SOC study hospitals,* the Wantai Screening HIV (1 + 2) Ag&Ab EIA (Beijing Wantai Manufacturer of Infectious Diseases Diagnostics) was used as the initial screening test followed by two different EIAs that varied between sites.

*In One4All study hospitals,* the first HIV screening test was the also the Wantai Screening HIV (1 + 2) Ag&Ab EIA. The second and the third EIAs were the Determine HIV-1/2^®^ rapid test (Abbott Laboratories) and the InTec HIV rapid test (Xiameng InTec Products).

#### HIV Confirmation

*In SOC study hospitals,* an additional blood sample was collected immediately following screening or on a subsequent study hospital visit. The sample was sent to the local city CDC laboratory for Western blot (WB) confirmatory testing according to usual practice. As confirmatory testing required approximately 10 to 15 days to be completed, participants typically had to be contacted and asked to return to the study hospital to receive their results.

*In One4All study hospitals,* WB was not used for confirmatory testing. Rather, VL testing served as the confirmatory test (see below).

#### CD4 Count

*In SOC study hospitals,* participants were asked to return to the study hospital for another blood draw for CD4 testing after they were notified that the result of their confirmatory testing was positive. Blood specimens were again sent to the city CDC laboratory, this time for CD4 testing. CD4 testing also required approximately 10 to 15 days to complete. Once CD4 test results were available, participants were again asked to return to be notified.

*In One4All study hospitals,* POC CD4 testing was performed in the study hospital with a POC Pima™ CD4 Analyzer (Alere Healthcare, USA) using whole blood samples. Results were available within 30 min. Participants were notified of their results as soon as possible, but no later than the next day if they had left the study hospital during the test.

#### Viral load

*In SOC study hospitals,* VL testing was conducted approximately one year after ART initiation. Participants were asked to return to the study hospital for blood sample collection. Blood samples were sent to the provincial CDC laboratory for plasma VL testing, which required 10 to 15 days to complete. Participants were contacted and asked to return to the study hospital to receive VL testing results once they were available.

*In One4All study hospitals,* blood samples for VL testing were collected immediately following receipt of positive screening results, at the same time as the blood draw for CD4 testing (see above). VL testing was conducted again after one year. Plasma VL testing itself was conducted in the same manner as in SOC study hospitals—samples were sent to the provincial CDC laboratory, plasma VL testing required 10 to 15 days, and participants asked to return to the study hospital to receive VL test results.

This intervention condition posed no specific safety risk to participants. In comparison to SOC study hospitals, the HIV care cascade in One4All study hospitals involved fewer blood draws and there was no increase in the volume of blood drawn or the typical risk associated with blood draws.

### Outcomes

The primary outcome measure was the proportion of participants who achieved testing completeness and received test results and post-test counseling within 30 days of positive screening. Testing completeness was defined as completion of three required components: 1) initial HIV screening (one to two tests in One4All and two to four in SOC), 2) CD4 testing, and 3) confirmatory HIV testing—WB in the SOC arm, or VL in the One4All arm. “Success” was defined as completion of all three required tests and notification of test result along with receipt of counseling after each test. Success was compared at 30 days after initial HIV-positive screening. The secondary outcome measure was the proportion of participants who initiated ART within 90 days from the date of HIV-positive screening. ART-initiation was defined as the receipt of the first ART prescription. Tertiary outcomes included the proportion of participants who achieved viral suppression (≤200 copies/mm^3^) and mortality at 12 months. Mortality was assessed as the number of reported deaths divided by the number of patients enrolled.

Aside from these main outcome measures, three other measures were pre-specified. For the primary outcome, two further analyses were planned: time from initial positive HIV screen to success, not restricted to the 30-day window, compared between control and intervention arms, and success at 45, 60, and 90 days, also compared between control and intervention arms. For the secondary outcome, one further analysis was planned: time from initial positive HIV screen to ART initiation, not restricted to the 90-day window, compared between control and intervention arms.

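### The success rule requires CD4 of every screen-positive enrollee, but standard care requests CD4 only after a positive Western blot, so a completed negative work-up fails in control and can succeed in One4All (minor bias)

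*Protocol article*

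**What the plan says.** - **Who is counted.** The eligibility criterion (Participants and recruitment) is "having a positive result on an HIV enzyme immunoassay (EIA) screening test", and the abstract says: "All patients screening HIV positive in study hospitals were enrolled". The only exclusion touching HIV status is previously confirmed infection. Nothing removes a person whose confirmatory test later proves negative.
- **What counts as success.** Under Outcomes, success "was defined as completion of all three required tests and notification of test result along with receipt of counseling after each test". The components are screening, CD4 and a confirmatory test, which is Western blot in SOC and viral load in One4All. CD4 is not made conditional on the confirmatory result.
- **When CD4 is offered in SOC.** Under CD4 Count, participants are asked back for "another blood draw for CD4 testing after they were notified that the result of their confirmatory testing was positive".
- **When CD4 is offered in One4All.** Under Viral load, the samples are "collected immediately following receipt of positive screening results, at the same time as the blood draw for CD4 testing". CD4 is read at the point of care, and viral load is the confirmatory test (HIV Confirmation).
- **Other uses of the definition.** Outcomes also plans comparisons of success at 45, 60 and 90 days and of time to success. Data analysis censors those who never meet the criteria at their last follow-up.

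**The concern.** The definition and the SOC pathway do not fit together for one group: people who screen positive and then have a negative Western blot. Once told the result and counseled, they have finished everything the described SOC pathway offers, yet they lack a CD4 test and are scored as failures. Their One4All counterparts have CD4 taken before any confirmatory result exists, so they can meet all three components.

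Faster CD4 testing in infected patients is a genuine benefit of One4All and should count. CD4 testing in people whose infection is not confirmed is not a benefit, and SOC should not lose credit for not requesting it. The error can only lower SOC success, which is the direction in which the one-sided test rejects. It also persists at later time points: as more SOC participants finish the Western blot work-up, q rises and the bias approaches its ceiling of f.

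**Working it through.** **Plan's own figure.** Inputs from Sample size: 180 per arm, 30 per hospital, ICC 0.082, proportions 0.50 and 0.22, one-sided alpha 0.05.

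- Design effect = 1 + 29 × 0.082 = 3.378.
- SE = √[3.378 × (0.50 × 0.50 + 0.22 × 0.78)/180] = √[3.378 × (0.25 + 0.1716)/180] = 0.0889.
- Power = Φ(0.28/0.0889 − 1.645) = 0.934, which reproduces the stated 93%.

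**Size of the bias.** SOC success is understated by f × q.

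- *f*, the share of SOC enrollees with a negative Western blot, is not in the documents. I assume 1–2%, show 0% and 5% as the ends of a range, and expect the low end because of repeat screening: the first assay "was used as the initial screening test followed by two different EIAs that varied between sites".
- *q*, the share of those people who finish Western blot, notification and counseling by day 30, is also not given. I use two proxies. The lower, 0.22, is the planned SOC success rate. Three-test success already includes these steps, so 0.22 is a floor if Western-blot-negative people return as often as others. The upper, 0.43, is the share of hospital screen-positives who received confirmatory testing (Background), with no time window.
- Laboratory time agrees with q at or above 0.22. For Western blot, "As confirmatory testing required approximately 10 to 15 days to be completed"; and "CD4 testing also required approximately 10 to 15 days to complete". Western blot alone therefore takes 10–15 days, against 20–30 days for the two in sequence.
- One4All needs no matching term, because CD4 blood is taken there regardless of the confirmatory result.

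**Rejection rate with no true effect.** Put both arms at 0.22 under an even-handed rule and score SOC at 0.22 − f × q. Then SE is about 0.08 and the rejection rate is Φ(f × q/SE − 1.645).

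**Power if the even rule is adopted.** This assumes the planned 0.22 used the three-test rule. Control becomes 0.22 + f × q and One4All stays at 0.50.

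| f (assumed) | f × q, q = 0.22 to 0.43 | People of 180 | Rejection, no true effect | Share of 0.28 | Power after change |
|---|---|---|---|---|---|
| 0% | 0 | 0 | 5.0% | 0 | 93% |
| 1% | 0.0022–0.0043 | 0.4–0.8 | 5.3–5.6% | 0.8–1.5% | 0.930–0.926 |
| 2% | 0.0044–0.0086 | 0.8–1.5 | 5.6–6.2% | 1.6–3.1% | 0.926–0.918 |
| 5% | 0.0110–0.0215 | 2.0–3.9 | 6.6–8.5% | 3.9–7.7% | 0.913–0.889 |

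**The case against.** **The size is assumed.** No confirmatory-negative share is given. At f = 1–2% the shift is at most about 1.5 people in 180. The choice of power formula matters more: one-sided power for this design is 0.934 unpooled, 0.923 pooled, 0.900 with a t reference on 10 degrees of freedom and 0.888 with a continuity correction. This stands, and it is why the point is minor.

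**The full protocol may settle it.** Dissemination says the original protocol is published elsewhere, and it could hold a rule for these people. That is possible. But the article states a complete success definition, and the point is how that stated rule works against the stated pathways.

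**SOC practice varied.** The Discussion says so, and says the case report forms were adapted to each hospital. Some control hospitals may have drawn CD4 earlier. The point therefore holds only for the cascades as described.

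**Any replacement rule has its own asymmetries.** An indeterminate Western blot can arise only in SOC. The confirmatory assays differ, so an infected One4All participant with undetectable viral load would be treated as negative. This stands in part. CD4 is taken at the same time there and read within 30 minutes, so the second case should seldom change a score. The first needs explicit handling.

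**The trial has been run.** The article is in the past tense and the trial was unblinded. Replacing a registered primary definition after outcomes are known would cost more credibility than a sub-point bias. This stands and governs the fix.

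**Conclusion.** The asymmetry is real under the cascades as described and favours One4All. It is minor: about 0.2–0.9 points at day 30 for f = 1–2% and q = 0.22–0.43, with a one-sided rejection rate of about 5.3–6.2% in place of 5%. It can never exceed f and vanishes if f is zero.

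Two stronger readings are tempting and are not supported. A reader might infer that the primary result could be an artefact of the definition. Even at f = 5% the bias is at most 7.7% of the planned 28-point difference, so it would not overturn an effect of that size; it would only add to a smaller one. A reader might also take the Background figure of 43% to mean that much of the remainder is confirmatory-negative. That figure counts people who received a confirmatory test and says nothing about results, and repeat screening points to a small f.

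**What to change.** Keep every enrollee in the denominator in both arms and score by one rule:

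- **Confirmatory result positive:** screening, confirmatory test and CD4, each notified and counseled within the window, as now.
- **Confirmatory result negative:** screening and confirmatory test, each notified and counseled within the window; CD4 not required.
- **No confirmatory test in the window:** failure, as now.

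Apply the rule at 30, 45, 60 and 90 days and to time to success. Do not restrict the analysis to confirmed infections: confirmation happens after randomization and uses different assays by arm.

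Make this the primary rule only by dated amendment and registry update before outcome data are seen, and report the original three-test definition alongside. Otherwise keep the registered definition as primary and report the even rule as a prespecified sensitivity analysis. Either way, report confirmatory-negative counts by arm and indeterminate Western blot counts, and score indeterminate results both ways, since that category exists only in SOC.

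Costs: no new test or visit. Confirmatory results must be available in the study data, and Data collection, management, and monitoring names only screening results explicitly, so this needs checking. Power falls from 93% to about 92–93% at f = 1–2%. The difference in confirmatory assays between arms remains. The rule does not help anyone cleared by repeat screening and never sent for a confirmatory test; the article does not say whether such people exist.
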